### Data Management and Analysis

The main outcomes in this study are contact, response, refusal, and completion proportions. Our outcomes are defined based on standard definitions from the 9th edition of the American Association for Public Opinion Research (AAPOR) [14], with some modifications to accommodate our RDD MPS design. Eligible individuals will be defined as persons who confirm that they are at least 18 years old.

Complete interviews (CI) are defined as age-eligible respondents who answer 5 or more modules. Partial interviews (PI) are defined as age-eligible respondents who answer between 2 and 4 modules. Participants who are age-eligible but answer less than 2 modules will be classified as a refusal/break-off (R). Non-contacts (NC) are defined as a confirmed number where respondent never picks up (this classification only applies to sub-studies 6 and 7). The main outcomes will be calculated using the equations in Figure 3.

Outcomes will be tabulated and stratified by both the question number and the question content due to the randomization of NCD topic modules. As a secondary analysis, we will conduct Kaplan-Meier curves to plot survey attrition by time spent on survey. For sub-study 7, test for agreement in survey responses between the survey modalities will be assessed using Cohen kappa. Statistical significance will be determined at an alpha of .05.

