### Proposed Sample Sizes

Assuming a baseline survey completion percentage of 30%, in order to detect an absolute 10% difference in survey completion between two study arms at an alpha of .05 and power of 80%, it is calculated that 376 individuals who have completed an IVR survey will be needed in each study arm for each sub-study. With a completion percentage of 30%, we calculated that 1254 participants would be required to consent to the survey per study arm in each country. With 16 study arms total in these 6 sub-studies, 20,064 participants will be enrolled in each country (Table 4). We have not inflated the sample size for multiple comparisons as per the recommendation by Rothman [12]. We chose a 10% difference between study arms as our preliminary analysis indicated that a 1 dollar incentive becomes cost-neutral at this cut-off point.

**Table 4 table4:** Number of participants needed to complete a mobile phone survey per country.

Sub-study	Study arms	Participants who completed survey per study arm, n	Total participants who completed the survey, n
Sub-study 1	3	376	1128
Sub-study 2	3	376	1128
Sub-study 3	3	376	1128
Sub-study 4	4	376	1504
Sub-study 5	2	376	752
Sub-study 6	1	376	376
Sub-study 7^a^	2	405	810
Total			6826

^a^For sub-study 7, we adjust for a 20% loss to follow-up from the first and second mobile phone survey.

For sub-study 7, the sample size is calculated based on the kappa statistic [13]. With assumption of kappa .75, a margin of error of 0.05%, an alpha of .05, and the proportion of positive responses of 0.3, 405 participants who have completed the survey per study arm are needed. Adjusting for a 20% loss to follow-up from the first and second mobile phone survey and a 30% baseline completion percentage, 1688 participants who consented will be enrolled per arm, for a total of 3376 participants across the two arms for each country.

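### Attrition plotted by Kaplan-Meier against minutes on the survey can run above the break-off proportion in its tail, and can separate arms that differ only in pace; question position or cumulative incidence avoids both

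*Protocol article*

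**What the plan says.** In the protocol article, Data Management and Analysis, one sentence sets this secondary analysis: "we will conduct Kaplan-Meier curves to plot survey attrition by time spent on survey". It fixes the estimator and the time axis. It does not define the attrition event, say how completers are handled, or name a comparison of curves between arms.

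The same section makes the plot subordinate to other results. "The main outcomes in this study are contact, response, refusal, and completion proportions", and "Outcomes will be tabulated and stratified by both the question number and the question content due to the randomization of NCD topic modules". Completion is counted in modules, not minutes: "Complete interviews (CI) are defined as age-eligible respondents who answer 5 or more modules".

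Some sub-studies change delivery by design. Sub-study 4 randomises the narrator's voice and the type of introduction, and Survey Delivery and Data Collection says that the motivational version carries extra wording. Sub-study 5 replaces a recorded introduction with a human operator, after which both arms take the IVR survey. Sub-study 7 compares IVR with CATI. Sub-studies 1 to 3 vary only the incentive.

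**The concern.** There are two separate difficulties.

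**Completion is not ordinary censoring.** Kaplan-Meier treats a censored person as someone who could still have the event later. A completer cannot break off later. If completers leave the risk set at their own finish times, the estimator in effect assumes that they would have gone on breaking off at the rate seen among the slower respondents who remain. One minus Kaplan-Meier then climbs past the true break-off proportion and need not agree with the completion proportion reported beside it.

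**Minutes are not the same as progress.** If one narrator speaks more slowly or one mode takes longer, respondents reach each question later. The same loss at each question is then spread over more minutes, and the slower arm looks better at any given minute. The objectives ask which introduction or mode keeps respondents, so a gap produced by pace could be misread as an answer.

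**Working it through.** **Inputs from the article (Proposed Sample Sizes).** "Assuming a baseline survey completion percentage of 30"%, so 70% do not complete. The design targets an "absolute 10% difference in survey completion between two study arms at an alpha of .05 and power of 80"%. The article gives 376 per arm and 1254 consenters per arm. The two-sided two-proportion formula for 30% against 40% gives 356 without and 376 with continuity correction, so 376 is reproduced. Then 376 / 0.30 = 1253.3, rounded up to 1254. The article states no figure for the attrition curve.

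**Assumptions.** The article gives no survey length, spread of durations or shape of drop-out. These are assumed below, and the range is shown.

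**Step 1: excess from censoring completers.** Break-off is exponential in the fraction of the survey reached, with probability 0.30 of reaching the end. Full duration is normal, mean 12 minutes, SD 2.5.

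| Minutes | 1 − KM, completers censored | Cumulative incidence of break-off | Excess (points) |
|---|---|---|---|
| 12 | 69.5% | 67.2% | 2.3 |
| 14 | 74.3% | 69.3% | 5.0 |
| 16 | 78.0% | 69.9% | 8.1 |
| 18 | 80.6% | 70.0% | 10.6 |

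At 8 minutes the two agree at 56%, and at 10 minutes they differ by less than 1 point. About 7% are still at risk at 14 minutes (0.07 × 1254 ≈ 88 people). With 1254 per arm, about 22 are at risk at 16 minutes and about 3 at 18 minutes.

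**Step 2: how the excess depends on the spread.** A second model has 30 questions of 0.5 minutes each and 30% completion, with drop-out per question either front-loaded or flat. One minus Kaplan-Meier is read where 1% remain at risk; the true value is 70%.

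| CV of pace | Front-loaded | Flat |
|---|---|---|
| 0 (all finish together) | 70% | 70% |
| 10% | 72% | 76% |
| 20% | 73% | 79% |
| 40% | 75% | 84% |

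The excess is zero before the first completion and zero if everyone finishes together. Otherwise it is about 2 to 14 points at that place in the tail. Cumulative incidence, or completers kept event-free in the risk set, ends at 70% in every setting.

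**Step 3: pace alone.** With flat drop-out and a survey of 30 × 0.5 = 15 minutes, attrition at minute t is 1 − 0.30^(t/L), where L is the arm's survey length. At t = 7.5:

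- L = 15: 1 − 0.30^(7.5/15) = 45.2%
- L = 16.5 (10% slower): 1 − 0.30^(7.5/16.5) = 42.1%
- L = 18 (20% slower): 1 − 0.30^(7.5/18) = 39.4%

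All three arms end at 70%.

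**Step 4: how visible such a gap is.** The article plans no test of the curves, so a log-rank test serves here only as a gauge. The settings are 1254 per arm, identical drop-out per question, CV of pace 10% and 500 simulated trials each. Rejection rates at the 5% level:

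| Second arm slower by | Time axis, flat | Time axis, front-loaded |
|---|---|---|
| 0% | 4% | 6% |
| 5% | 17% | 8% |
| 10% | 49% | 11% |
| 20% | 95% | 27% |

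On a question-number axis rejection stays at 3–6%, and the test of completion proportions stays at 3–7%, whatever the pace. If one arm's introduction adds 0.25, 0.5 or 1 minute and that time is counted, the time-axis rates are 7%, 18% and 63% (flat drop-out, 300 simulated trials each).

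**The case against.** The strongest reply is that the article does not contain the error. A reader might infer that the plan censors completers and so overstates attrition. The article does not say so: a condensed report commonly leaves event and censoring rules to the full protocol or analysis plan, and keeping completers event-free would remove the excess. That stands, so the first part of the point is conditional.

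A reader might also infer that the curves will show arm differences that do not exist. That goes too far. A curve in minutes correctly describes time to break-off, which is a fair question when choosing a survey length, and no between-arm comparison of curves is stated. The error arises only if a gap in minutes is read as a gap per question.

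Nor is this the only view of where people leave. The article tabulates outcomes by question number and content, classifies respondents by modules answered, and calls back a sample of those who consented but did not complete. Language is chosen by the respondent and is not an arm, so randomisation should roughly balance it.

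Finally, the larger excesses in Step 1 sit where few people remain, and every duration is assumed. That also stands. What survives is that the article does fix Kaplan-Meier and elapsed time, that completion does end the risk, and that a pace-neutral axis is available from data already planned.

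**Conclusion.** The point holds as a minor improvement to a secondary, descriptive analysis. If completers are censored at varying finish times, the curve overstates break-off in its tail: about 2 points at the assumed 12-minute mean and about 2 to 14 points where 1% remain at risk, for a CV of pace of 10–40%. There is no overstatement before the first completion. The size cannot be fixed from the article because the spread of durations is not given.

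Separately, minutes are not pace-neutral in sub-studies 4 and 7, nor in sub-study 5 if introduction time is counted. A 10–20% difference in pace would open a mid-survey gap of about 3 to 6 points under flat drop-out, and less consistent separation if drop-out is front-loaded. The article supports no particular pace difference between arms. Little effect is expected in sub-studies 1 to 3.

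The contact, response, refusal and completion proportions and the sample size do not depend on the curve. The documents do not support a reading that the trial's main comparisons are biased.

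**What to change.** - Show the attrition curve as the proportion remaining by question or module position. Completion is already defined by modules answered, so on the same denominator this curve can be checked directly against the completion proportion. Module order is randomised, so position and content should be kept distinct, as the planned tabulation already does.
- If a curve in minutes is also wanted, use the cumulative incidence of break-off (Aalen-Johansen) with completion as a competing event, or keep completers event-free in the risk set. State the event, when the clock starts, and whether introduction time counts.
- Add a sentence that gaps between arms on the time axis in sub-studies 4, 5 and 7 are not to be read as differences in break-off per question.

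The cost is analysis code and a few lines of text. No extra data or participants are needed.

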## Introduction

Effective prevention and control of non-communicable diseases (NCDs) centers on surveillance and reduction of exposure to risk factors that give rise to these conditions. Four behavioral, and largely modifiable, risk factors account for the majority of NCDs: unhealthy diet, tobacco use, inadequate physical activity, and excessive use of alcohol [1]. Surveillance provides crucial information on disease burden to guide resource planning and allocation and evaluation of public health interventions and programs [2]. Unfortunately, many low- and middle-income countries (LMICs) face the challenge of implementing effective and systematic ways of tracking NCD risk factors and collecting timely and high-quality data. The rise of mobile phones in LMICs presents an opportunity to use this technology to aid NCD risk factor data collection. Currently, worldwide mobile phone subscriptions have reached 99.7 subscriptions per 100 persons, with 94.1 subscriptions per 100 persons in LMICs [3].

High levels of mobile phone access and ownership afford new opportunities to conduct surveys. As a complement to household surveys, respondents can be interviewed over their personal mobile phones. The most common types of mobile phone surveys (MPSs) are short message service (SMS), computer-assisted telephone interview (CATI), and interactive voice response (IVR). In CATI, an interviewer questions the respondent over the phone. With SMS, brief text messages are used to communicate between devices [4]. In IVR, users interact with a database programmed with questions and a series of pre-recorded answers to the questions, linked to a specific numeric key or numeric response on a touch-tone phone keypad (eg, “Press 1 if you are male, press 3 if you are female”).

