### Evaluation Phase

#### Setting and Participants

The research activities will be implemented in Bangladesh, Tanzania, and Uganda. Information on collaborating partners, mobile phone subscription rates [7], mobile network operators (MNOs), and survey languages is summarized in Table 1. The term “subscription” in Table 1, and throughout this protocol, refers to different forms of mobile phone ownership including monthly subscriptions and pre-payment options which are common in LMICs.

**Table 1 table1:** Country partners, survey languages, and mobile phone subscriptions in each country.

Country	Mobile phone subscriptions per 100 people, n	Mobile network operators in country, n	Implementing partner	Languages for mobile phone survey
Bangladesh	83	5	Institute of Epidemiology, Disease Control and Research (IEDCR)	Bangla, English
Tanzania	76	5	Ifakara Health Institute (IHI)	Kiswahili, English
Uganda	50	6	Makerere University School of Public Health (MakSPH)	Luganda, Runyakitara, Luo, English

In each of the 3 countries, participants for the MPS, except for sub-study 6, will be selected through random digit dialing (RDD) [8]. For each country, we will identify all active MNOs and their respective prefixes that lead a 10-digit mobile phone number. Using these unique prefixes, the remaining digits will then be randomly generated via a computer to create a random sample of mobile phone numbers to which the surveys will be delivered (Table 2). Participants that are selected using RDD will be asked to provide consent and their age. Participants who do not indicate their age or report being less than 18 years old will be excluded from the study.

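### Sub-study 7 names Cohen kappa as its only agreement statistic and sizes it on a yes/no item; for any ordered or numeric answers it is the wrong measure, and the text should limit it by item type.

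*Protocol article*

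**What the plan says.** Under Data Management and Analysis, the article gives one statistic for inter-modal reliability in sub-study 7: "test for agreement in survey responses between the survey modalities will be assessed using Cohen kappa". It mentions no weighting and no separate measure for ordered or numeric answers.

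Under Proposed Sample Sizes, the number of participants is tied to the same statistic: "For sub-study 7, the sample size is calculated based on the kappa statistic". The inputs are given as "With assumption of kappa .75", "a margin of error of 0.05" (printed with a percent sign) and "an alpha of .05, and the proportion of positive responses of 0.3". The last input defines a two-category item. The result is 405 completers per arm, 810 in Table 4, and 1688 consenting participants per arm.

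On answer formats the article says little. The Introduction describes IVR answers as "linked to a specific numeric key or numeric response on a touch-tone phone keypad". Setting and Participants says "Participants that are selected using RDD will be asked to provide consent and their age". The Questionnaire section names the topics (physical activity, alcohol, tobacco, diet) and the standard surveys from which questions were drawn. It does not list items or response scales.

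**The concern.** Cohen kappa in its ordinary form treats answers as unordered categories. On a 0 to 7 scale, answering 3 in one modality and 4 in the other counts as just as complete a disagreement as answering 0 and 7. If the questionnaire has ordered or numeric items, an analyst who follows the stated method has two choices. The levels can be kept, in which case kappa falls as their number rises even though the underlying reliability is unchanged. Or the item can be cut to yes/no, in which case kappa is interpretable but information already collected is discarded.

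This matters because inter-modal reliability is part of the article's fourth objective, an added outcome of sub-study 7, and the quantity on which that sub-study is sized. A graded item on which IVR and CATI answers are nearly always close could be reported as showing only moderate agreement.

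**Working it through.** **1. Reproduce the plan's figure.** Inputs from Proposed Sample Sizes: κ = 0.75, p = 0.3, two-sided α = .05 (z = 1.96), margin d = 0.05 on the kappa scale. The printed percent sign cannot be meant, since only 0.05 gives the stated number.

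Large-sample variance of binary kappa with equal margins, per pair:

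V = (1−κ)[(1−κ)(1−2κ) + κ(2−κ)/(2p(1−p))]

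= 0.25 × [0.25 × (−0.5) + (0.75 × 1.25)/(2 × 0.3 × 0.7)]

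= 0.25 × [−0.125 + 0.9375/0.42] = 0.25 × 2.107 = 0.5268

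n = z²V/d² = 3.8415 × 0.5268/0.0025 = 809.5, so 810 pairs. This is the Table 4 total, or 405 per arm. Inflation: 405/0.8/0.3 = 1687.5, so 1688 per arm, as stated. The size is therefore that of a yes/no item. The margin of 0.05 is met by pooling both arms: 1.96 × √(0.5268/810) = 0.050. One arm alone gives 1.96 × √(0.5268/405) = 0.071.

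**2. Same reliability, more levels.** Assumptions (the documents give no item distributions): a bivariate normal latent answer in the two modalities, equal-frequency categories, and 3, 5 or 8 levels as an illustrative range. The latent correlation is chosen so that a cut at 30% positive gives the plan's κ = .75. That correlation is r = 0.929.

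With K equal-frequency categories, chance agreement is 1/K, and unweighted kappa is (Po − 1/K)/(1 − 1/K), where Po is the share of identical answers under the model:

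- 3 levels: Po = 0.781, (0.781 − 0.333)/0.667 = .67
- 5 levels: Po = 0.624, (0.624 − 0.2)/0.8 = .53
- 8 levels: Po = 0.471, (0.471 − 0.125)/0.875 = .40

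Linear weights are 1 − |i−j|/(K−1). Half-widths use the Fleiss-Cohen-Everitt variance with 810 pairs.

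| Item | Unweighted kappa | Linear-weighted kappa | 95% half-width, linear-weighted, 810 pairs |
|---|---|---|---|
| 3 levels | .67 | .75 | 0.034 |
| 5 levels | .53 | .75 | 0.026 |
| 8 levels | .40 | .75 | 0.022 |
| Cut to yes/no, 30% positive | .75 | not applicable | 0.050 (unweighted) |

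Under the same model, 97% of pairs (5 levels) and 88% (8 levels) lie within one category of each other.

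**3. Check under a different error model.** Take a uniform 0 to 7 item where 30%, 50% or 70% of repeat answers are shifted by one unit (shifts beyond the ends of the scale are held at the end). Unweighted kappa is 0.70, 0.50 and 0.30; linear-weighted kappa is 0.90, 0.83 and 0.77. The direction is the same, and the size depends on how often answers move.

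**4. Cost of a yes/no cut.** With 810 pairs, 0.050/0.026 = 1.9 and 0.050/0.022 = 2.3. The interval is roughly twice as wide as that of linear-weighted kappa on 5 or 8 levels.

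**The case against.** The strongest reply is that the article shows no ordered or numeric risk-factor item. The phrase about numeric responses is a general description of IVR, and its example, male or female, is nominal. Age is asked for eligibility, as a screening step separate from the risk-factor modules. Response options are to be settled in the formative phase, the text does not exclude weighted kappa, and assigning a statistic to each item can sit in the full protocol or analysis plan. The sizing on a proportion positive is coherent if the target is agreement on yes/no risk-factor status.

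Much of this stands, and it limits the point. It cannot be said that every answer will be analysed with unweighted kappa, or that any particular item will be misjudged. What remains is that the article does fix a statistic, for survey responses without distinction, and that this statistic is a poor one for ordered or numeric answers, which the text allows for and these topics make likely.

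A reader might infer three stronger things that the documents do not support:

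- *That the sample size is wrong.* It is right for a yes/no item, and the pooled 810 pairs meet the planned margin. The half-width of 0.071 belongs to one arm alone.
- *That items will be ranked by kappa.* Nothing in the article ranks items or compares kappa between items with different numbers of options.
- *That weighting brings a large gain in power to compare the two orders of administration.* The article mentions adjustment for priming but specifies no test of kappa between orders. Under the model above the gain also vanishes at 3 levels (74% unweighted against 75% weighted).

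Weighted kappa is not free of choice either: at 8 levels and the same reliability it is about .75 with linear weights and .91 with quadratic weights. That is a reason to fix the weights beforehand.

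**Conclusion.** The point holds in a conditional form. Cohen kappa is the only agreement statistic named for sub-study 7, it is sized on a yes/no item, and it suits yes/no and nominal items. To the extent that the questionnaire has ordered or numeric answers, it understates agreement if the levels are kept: about .67, .53 and .40 for 3, 5 and 8 levels, where linear-weighted kappa stays near .75. If the items are cut to yes/no, the interval is about twice as wide as it need be with 5 or 8 levels.

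These sizes rest on the bivariate normal model, equal-frequency categories, the assumed numbers of levels and the plan's own κ = .75. With 3 levels the understatement is modest. The point touches only the reliability part of sub-study 7. It leaves the contact, response, refusal and completion outcomes unaffected. The change is worth making before analysis because it costs almost nothing.

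**What to change.** In Data Management and Analysis, state the agreement measure by item type:

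- yes/no and nominal items: Cohen kappa, as now;
- ordered-category items: weighted kappa with the weights fixed in advance, for example linear, with quadratic as a sensitivity analysis;
- numeric items: an intraclass correlation for absolute agreement, with the mean IVR minus CATI difference and limits of agreement.

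In Proposed Sample Sizes, add that the calculation with kappa .75 applies to yes/no items.

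The cost is a few sentences and slightly more analysis, with no extra participants or data. The drawback is that reliability is then reported on more than one scale, so items of different types cannot be set side by side on a single number.

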#### Sub-Study 7: Survey Modality

This sub-study evaluates the effect of the survey modality (IVR versus CATI) on the survey’s response and completion rates and assesses the inter-modal reliability. Participants will be randomized to 1 of 2 arms: (1) IVR then CATI; or (2) CATI then IVR. Participants in the first study arm will receive an IVR survey first, followed by a CATI survey 7 days later (Figure 1). Participants in the second study arm will receive a CATI survey first followed by an IVR survey 7 days later. At initial enrollment, it will be clearly explained to participants that they are being enrolled in a study where they will be contacted twice. The questionnaires used in both study arms will be the same. This crossover design will allow for an assessment of response consistency, adjusted for the risk of “priming” after exposure to the prior modality. This is the only sub-study that will require participants to answer the NCD survey twice. The amount, timing, and structure of incentive will be guided by the first 3 sub-studies where the incentive that yielded the highest response and completion rates will be provided to all participants in sub-study 7. This sub-study will be conducted in Bangladesh and Tanzania.

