## Discussion

National public health surveillance in many LMICs have typically centered on communicable diseases [9]. The emerging burden of NCDs means that many LMICs have to work quickly to set up effective surveillance systems to curb the epidemic. Faced with greater resource constraints than high-income countries, there is need for cost-effective and timely surveillance methods in LMICs. MPSs have the potential to enhance current efforts for systematic collection of NCD risk factor data to identify national trends, as well as to identify segments of the population at particularly high risk for NCDs. If properly harnessed, MPSs have potential to assist LMIC policy makers with resource allocation and choice of NCD prevention and control interventions, among other decisions [15].

The systematic examination of selected incentive characteristics has two potential benefits. First, the optimization of incentive structure and amounts will increase the survey’s contact, response, and completion rates; thereby reducing the number of calls needed to achieve the desired sample size. Second, and only if incentives do not have a differential effect on sub-groups of respondents (ie, incentives increase response in those with more education or of higher socio-economic status), higher response and completion rates may potentially reduce non-response bias.

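### Sub-study 7: Cohen kappa, the only IVR-CATI agreement statistic named, barely reacts to a one-way mode shift, so a paired prevalence difference should be reported beside it

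*Protocol article*

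**What the plan says.** Sub-study 7 randomises participants to IVR then CATI or CATI then IVR, 7 days apart, with the same questionnaire. Its section gives the aim as the effect of modality on the "survey’s response and completion rates and assesses the inter-modal reliability". It adds: "This crossover design will allow for an assessment of response consistency, adjusted for the risk of “priming” after exposure to the prior modality".

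Data Management and Analysis gives the agreement analysis in one sentence: "test for agreement in survey responses between the survey modalities will be assessed using Cohen kappa". The next sentence reads "Statistical significance will be determined at an alpha of .05". No kappa value is set above which the modes count as reliable.

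Proposed Sample Sizes also builds on kappa: "With assumption of kappa .75, a margin of error of 0.05%, an alpha of .05, and the proportion of positive responses of 0.3", from which "405 participants who have completed the survey per study arm are needed".

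The other planned mode comparisons (Introduction, objective 4; Study Design) concern contact, response, completion and refusal rates and demographic representativeness. They do not concern the risk-factor answers.

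**The concern.** Disagreement between two modes has two parts. Answers that flip equally in both directions are noise and cancel in a prevalence estimate. Answers that flip mainly one way move the prevalence. Kappa depends on the total number of disagreements and hardly on their direction.

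The direction matters for the use that the article has in view. Its Discussion says that "MPSs have the potential to enhance current efforts for systematic collection of NCD risk factor data to identify national trends". If IVR reads systematically higher or lower than CATI on an item, a switch of mode would look like a change in the risk factor, even with a respectable kappa. The design collects what is needed to see this, but the statistic that the article names would not show it.

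**Working it through.** **Inputs.** Proportion positive p = .30, kappa k = .75, two-sided alpha .05, 405 completers per arm in each country, 20% loss to follow-up and 30% completion (all from Proposed Sample Sizes). The margin is printed as 0.05%. It is read here as d = 0.05 on the kappa scale, because that value reproduces the sample size.

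**Step 1: reproduce the plan's figure.** Large-sample formula for a binary item with common prevalence:

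n = z²(1−k)[(1−k)(1−2k) + k(2−k)/(2p(1−p))]/d²

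= 3.8415 × .25 × [.25 × (−.5) + .9375/.42]/.0025 = 809.5

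That is 810 pairs, or 405 per arm with both arms pooled. Enrolment: 405/.8/.3 = 1687.5, so 1688 per arm. Both stated figures reproduce.

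**Step 2: discordance implied by the plan.** Chance agreement Pe = .3² + .7² = .58. Observed agreement Po = .58 + .75 × .42 = .895. So 10.5% of pairs are discordant.

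**Step 3: change the direction and keep the amount.** Hold Po at .895, so that kappa = (.895 − Pe)/(1 − Pe). With margins p₁ and p₂, Pe = p₁p₂ + (1−p₁)(1−p₂). The paired test statistic with 810 pairs is z = (b − c)√810/√(b + c), where b and c are the two discordant proportions and b + c = .105.

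| Discordant split | Prevalence by mode | Pe | kappa | paired z |
|---|---|---|---|---|
| 5.25% / 5.25% | 30.0% and 30.0% | .58000 | .750 | 0 |
| 7.75% / 2.75% | 32.5% and 27.5% | .57875 | .751 | 4.4 |
| 10.5% / 0, centred on 30% | 35.25% and 24.75% | .5745 | .753 | 9.2 |
| 10.5% / 0, one mode at 30%, other higher | 30.0% and 40.5% | .538 | .773 | 9.2 |
| 10.5% / 0, one mode at 30%, other lower | 30.0% and 19.5% | .622 | .722 | 9.2 |

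When the two modes average 30%, Pe = .58 − g²/2 for a prevalence gap g. The gap enters only through its square, and kappa rises slightly as the gap grows. All five values lie within .75 ± .05.

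**Step 4: what the planned data can show.** The 95% half-width of the paired difference is 1.96 × √(.105/810) = .022, about 2.2 points. For one order alone it is 1.96 × √(.105/405) = .032, about 3.2 points.

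For the first survey only, 405/.8 = 506 completers per arm give a between-arm half-width of 1.96 × √(2 × .21/506) = .056, about 5.6 points.

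**Step 5: what a significance test adds.** The null hypothesis for kappa is not named. If it is kappa = 0 (an assumption), the null standard error at equal 30% margins is 1/√810 = .035 and z = .75/.035, about 21. Significance would be reached in any case and would say nothing about direction.

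**The case against.** The strongest objection is that this is an omission in a condensed article. One sentence names the principal statistic, and item-level comparisons may stand in a full protocol or analysis plan that is not shown. Kappa is a standard measure of reliability, and reliability is the stated aim. Equality of prevalence is a different quantity, and the Discussion text on national trends is not an aim of this sub-study. The remark on priming suggests that some analysis by order is intended.

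Much of this stands. The article does not exclude a comparison of prevalences, so it cannot be said that none will be made. What remains is that the article chooses kappa as the agreement analysis and sizes the sub-study on it, and that this statistic cannot show the direction of disagreement.

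A reader might infer that a biased mode would be passed as reliable. The documents do not support that. They give no pass mark and no rule on substituting one mode for the other, and .75 is a planning value for precision.

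A reader might also infer that kappa is always the same with or without bias. It is so to two decimals only when the two modes average 30%; otherwise the extreme case gives .722 or .773.

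The 10.5-point gap is itself the extreme, since every discordant pair must run one way. Kappa does bound the bias, because at a given prevalence the gap cannot exceed the discordance rate. But the bound is loose, and the 5-point case needs only 7.75/10.5 = 74% of discordant pairs to run one way.

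**Conclusion.** The point holds as a limit on what sub-study 7 can conclude. The one agreement statistic named moves by .001 for a 5-point mode shift and by .003 for a 10.5-point shift centred on 30%. In the cases with one mode held at 30% it moves by less than .03. All of this is smaller than the planned margin of 0.05, so a good kappa would be compatible with a systematic difference between modes.

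The sizes rest on a binary item at the plan's 30% prevalence, on kappa .75, and on 810 complete pairs per country. They do not show that a mode shift exists, nor that the plan contains a wrong decision rule. This is a worthwhile and cheap improvement, not a fault in the design.

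**What to change.** In Data Management and Analysis, keep Cohen kappa and add for each item the paired IVR minus CATI difference in proportion (mean difference for numeric items) with a 95% confidence interval, shown for each order and averaged over the two orders. Averaging cancels a common period effect. It does not remove priming that differs between the orders, so the results by order should be shown as well.

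The between-arm difference in first-survey answers may be given as a supplement. It precedes exposure to the other mode, but it mixes mode effects with who responds. Its figure of 506 per arm also assumes 30% completion in both modes, although completion by mode is itself an outcome.

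No joint criterion of high kappa and small difference is needed unless both terms are defined in advance.

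The cost is analysis wording and some extra tabulation of data already collected. The downside is that some items with a good kappa may be reported as shifted between modes.
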